## Abstract

**Background:**

Stimulant use disorder has been linked with medication nonadherence and mortality among people living with HIV. Contingency management (CM) is a strategy incentivizing measurable behavior change that is recommended as the first-line treatment for stimulant use disorder and can support antiretroviral therapy (ART) adherence. However, CM is not widely implemented, in part due to feasibility concerns. Although reductions in substance use short of full abstinence can improve health outcomes, CM programs typically target complete abstinence from stimulant use rather than reduction. To optimize care for safety-net populations living with comorbid stimulant use disorder and HIV, we designed a novel CM program incentivizing both stimulant use reduction and ART adherence in the HIV ambulatory setting.

**Objective:**

We aimed to (1) evaluate the feasibility of once-weekly CM in safety-net HIV ambulatory care and (2) assess the acceptability of CM among participants and care providers.

**Methods:**

We will conduct a pilot, single-arm, hybrid implementation effectiveness trial offering a novel CM intervention in 2 low-barrier, ambulatory HIV clinics. Patients with stimulant use disorder and suboptimal ART adherence will be offered 12 weeks of once-weekly CM including incentives for positive-tenofovir and negative-stimulant results on urine point-of-care assays. We will assess stimulant use once weekly using tests with a 4-day detection window, allowing participants to use stimulants during select days of the week but earn incentives by reducing their frequency of use from near-daily use. We will assess feasibility and acceptability using quantitative process methods and qualitative in-depth interviews, guided by the RE-AIM (reach, effectiveness, acceptability, implementation, and maintenance) evaluation framework. We will define preliminary effectiveness by proportion of stimulant-negative and tenofovir-positive urine tests, as well as changes in HIV viral suppression before and after participation.

**Results:**

Recruitment and CM visits have concluded as of September 2024. Quantitative and qualitative evaluation is underway and is expected to continue through October 2025.

**Conclusions:**

This novel CM program offers dual incentives targeting stimulant use reduction and ART adherence. We hypothesize that incentivizing stimulant use reduction is acceptable to our target safety-net population. Demonstration of a feasible, acceptable model may serve as a first step toward wider use of stimulant-reduction CM in the safety-net setting.

**Trial Registration:**

ClinicalTrials.gov NCT06564792; https://clinicaltrials.gov/study/NCT06564792

**International Registered Report Identifier (IRRID):**

DERR1-10.2196/67292

## Introduction

### Background

Stimulant use disorder continues to rise as a devastating public health issue in the United States, accounting for more than 57,000 deaths in 2022—a near 5-fold increase since 2015 [1] Among people living with HIV, stimulant use is particularly prevalent (>5% to 15% in the general population of people with and 30% in safety-net patient populations living with HIV) and represents a key challenge for maintaining overall health [2-4]. Both methamphetamine and cocaine have been repeatedly associated with antiretroviral therapy (ART) nonadherence, HIV viremia, and progression to AIDS; by some estimates, people living with HIV using stimulants demonstrate double the odds of ART nonadherence compared to those not using stimulants [5-9].

Contingency management (CM) is the first-line treatment for stimulant (methamphetamine and cocaine) use disorder and has also been used to promote ART adherence for people living with HIV [10-15]. This behavioral treatment—in which patients receive tangible incentives for demonstrating abstinence (eg, measured by drug-negative urine)—is highly efficacious, supported by a multitude of randomized controlled trials [10,16,17]. In addition, research suggests that CM can also be efficacious for ART adherence, although these studies were limited by the potential inaccuracy of indirect adherence measurements (eg, electronic pill bottle cap monitoring does not equate to ingested medication) [11-15].

Despite its demonstrated efficacy, the uptake of CM remains limited in both safety-net and ambulatory settings. While these settings represent the main source of medical care for many high-need patients, feasibility concerns have largely impeded CM implementation. Frequently described barriers include insufficient training and awareness, logistic concerns related to program execution, cost and resource intensiveness of programs requiring multiple weekly visits, and staff reluctance to provide financial incentives [18-21]. In addition, addressing syndemic behaviors simultaneously (by incentivizing both stimulant use reduction and ART adherence through a single “multitarget” intervention) is an important opportunity to seize. To effectively reach people living with HIV who are most in need of this treatment, there is an urgent need for feasible CM models that target stimulant use and ART adherence in ambulatory safety-net settings.

Leveraging harm reduction principles will be essential for addressing the needs of safety-net populations with comorbid HIV and stimulant use disorder. Abstinence from stimulants can be an unrealistic, unwanted, or a less proximate goal for people with severe stimulant use disorder, who may be using daily or chronically [22]. Efforts to emphasize stimulant use reduction rather than abstinence have shown promise in promoting overall health; for example, in a secondary analysis of 13 randomized controlled trials, reduced use of methamphetamine and cocaine was associated with global improvement of psychosocial functioning and severity of drug-related problems, as well as improved depression and fewer drug-seeking behaviors [23]. Although CM is traditionally structured to promote abstinence, new models that incentivize stimulant use reduction and other positive health behaviors may be more aligned with patient goals and needs in the safety-net setting.

To optimize care for safety-net populations living with comorbid stimulant use disorder and HIV, we designed a novel CM program incentivizing both stimulant use reduction and ART adherence in the HIV ambulatory setting, called CoMBo (Contingency Management for Both HIV and Stimulant Use Disorder). CoMBo involves point-of-care (POC) tests that detect stimulant use within a 3- to 4-day window and offer once-weekly visits in contrast to traditional CM programs that test urine 2 to 3 times per week to confirm abstinence. In addition, we use a novel POC, a urine-based tenofovir assay that allows for real-time assessment of adherence to tenofovir-based ART [24,25]. This technology enables simultaneous assessment of tenofovir adherence and stimulant use by using one urine sample, facilitating a truly paired intervention.

In this paper, we present a full description of an implementation effectiveness pilot delivering CM with paired incentives in the HIV ambulatory setting and describe a protocol for the quantitative and qualitative evaluation of program feasibility and acceptability (the CoMBo study). We hypothesize that (1) this program will be acceptable to staff and participants and (2) offering once-weekly CM (as opposed to multiple-times per week) to achieve stimulant reduction (as opposed to abstinence) in low-barrier medical homes of people living with HIV will be feasible.

### CoMBo Study Objectives

The following are the objectives of this study:

To evaluate the feasibility of once-weekly CM in safety-net HIV ambulatory care to decrease stimulant use and improve ART adherenceTo qualitatively assess the acceptability of CM offered in safety-net HIV ambulatory care to participants and care providers

## Methods

### CoMBo Study Design

We will conduct a pilot, single-arm, hybrid implementation effectiveness trial of dual-incentive CM targeting stimulant use reduction and improved ART adherence in 2 low-barrier, ambulatory HIV clinics. We use the Behavior Change Wheel framework to tailor this intervention to meet the needs of our target safety-net population (Table 1). This study design will allow for the investigation of implementation feasibility in our target setting, while also gathering data on the intervention’s impact on target behaviors. The study will occur over a period of 9 months; patient recruitment will occur during the first 6 months of the study on a rolling basis. Following this pilot, we will solicit feedback on intervention acceptability using in-depth qualitative interviews with participants and clinic staff. The study has been registered as a clinical trial (ClinicalTrials.gov NCT06564792).

**Table 1 table1:** Formative intervention components for targeting behavior change in safety-net ambulatory care, as described by the Behavior Change Wheel framework [26].

Source of behavior	Example of barriers to behavior change	Intervention component	How will intervention component facilitate behavior change?
Motivation (reflective and automatic)	Complete abstinence following a long period of dependence may be unrealistic, intimidating, or unwanted	1. Assess stimulant use reduction using once weekly using point-of-care tests with a 2- to 4-day detection window	Incentivization: create expectation of reward
Motivation (reflective)	Internalized stigma around psychosocial factors (eg, substance use and housing instability) leads to low self-belief in ability to change behavior	2. Engage in motivational interviewing, emphasizing self-talk and goal setting and providing social support	Persuasion: induce positive or negative feelings to stimulate actions
Opportunity (physical and social)	Limited resources to schedule and keep consistent in-person appointments (eg, limited access to phone, transportation)	3. Offer drop-in, one-on-one visits	Environmental restructuring: change physical and social context

### Study Setting

This study will be conducted at 2 subclinics at San Francisco General Hospital’s Ward 86, one of the oldest HIV clinics in the country serving more than 2600 people living with HIV in the county safety net. Ward 86 provides wraparound care with co-located behavioral health, social work, case management, laboratory, and pharmacy services. The Women’s Clinic is an interdisciplinary, team-based model of care providing HIV, substance use disorder, drop-in services, and mental health care to people identifying as cis- or transwomen living with HIV at Ward 86, serving 234 patients as of July 2022. The POP-UP clinic is another interdisciplinary, team-based clinical program within Ward 86 providing low-barrier, drop-in primary care to patients with HIV experiencing homelessness. At least 30% of the Ward 86 population report regular stimulant use, with approximately 40% of Women’s Clinic patients and 90% of POP-UP patients reporting stimulant use. By co-locating CM into low-barrier medical homes for vulnerable people living with HIV, we aim to decrease barriers to CM engagement for patients with comorbid stimulant use disorder and HIV.

### Study Population and Inclusion and Exclusion Criteria

Recruitment, enrollment, and study procedures will occur at Ward 86, with targeted recruitment from the aforementioned clinics. We aim to recruit participants living with HIV who (1) are on tenofovir-based ART regimens, (2) are diagnosed with severe stimulant use disorder (according to the *Diagnostic and Statistical Manual of Mental Disorders, Fifth Edition* criteria, measured with the Structured Clinical Interview for DSM-5, using at least near daily), (3) have suboptimal ART adherence (defined as at least one instance of HIV viral load over 200 copies/mL in the preceding 18 months or reporting periods of discontinuation within last 18 months), (4) are interested in reducing frequency of stimulant use and improving ART adherence, and (5) speak either English or Spanish [26]. On the basis of the estimated prevalence of comorbid stimulant use disorder and HIV within our target safety net, we aim to recruit approximately 40 participants.

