### Evaluation Frameworks and Outcomes

#### Quantitative Evaluation

We will leverage the RE-AIM (reach, effectiveness, adoption, implementation, and maintenance) framework (Table 3) to quantitatively evaluate feasibility, reach, effectiveness, and intervention implementation.

Per our first study objective, we aim to evaluate the feasibility of implementing this intervention in the safety-net, ambulatory HIV care setting, which we will assess using various domains of the RE-AIM evaluation framework. Our primary outcome will be defined via engagement: 50% CM visit attendance will indicate a threshold for program feasibility. Secondary feasibility outcomes will include number of visits performed, average visit time, and monetary value earned per participant, which map to domains (Table 3). Metrics related to “reach” will assess if the proposed implementation model will be used by a diverse patient population with complex sociomedical needs (as intended), reflecting both the utility and accessibility of this program. “Effectiveness” metrics will seek to establish if the intervention modified the target behavior changes, leading to reduced stimulant use, improved ART adherence, and undetectable HIV viral loads. “Implementation” metrics will describe the costs required to start and maintain this program during the study period (8 months). Our secondary outcome is preliminary effectiveness, which we will determine using proportion of stimulant-negative and tenofovir-positive urine tests, as well as changes in HIV viral suppression before and after participation. We will report missing data and impute missing viral load data as >200 copies/mL.

**Table 3 table3:** RE-AIM (reach, effectiveness, adoption, implementation, and maintenance) framework evaluation of dual-incentive contingency management targeting antiretroviral therapy adherence and stimulant use in ambulatory HIV care.

Dimension	Question	Outcomes
Reach	Will safety-net patients living with HIV and stimulant use disorder enroll in this program? Will they return after enrollment?	Sociodemographics Substance use and HIV histories Proportion of study visits attended
Effectiveness	Will participants reduce stimulant use? Will participants improve tenofovir adherence?	Weekly point-of-care results and 7-d timeline follow-back

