### Analysis Plan

#### Quantitative Evaluation

We will analyze reach and implementation metrics (Table 3) using basic descriptive statistics. For effectiveness, we will use descriptive statistics to describe POC results, including the proportion of negative-stimulant and positive-tenofovir tests each week and cumulatively overall and the number of participants that test negative for stimulants or positive for tenofovir at least once. We will also report the average frequency of use as captured by weekly timeline follow-back and compare average use at baseline versus study visit 12 (ie, the final visit) using a paired 2-tailed *t* test. We will use the McNemar test to compare the proportion of participants with HIV viral loads less than 200 copies/mL before and after CM participation.

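### Setting missing viral loads to >200 copies/mL turns participants already suppressed at entry into apparent losses, and the pooled McNemar test nets these against real gains

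*Protocol article*

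**What the plan says.** Four statements in the protocol article combine here.

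- **Entry** (Study Population and Inclusion and Exclusion Criteria). The adherence criterion is "at least one instance of HIV viral load over 200 copies/mL in the preceding 18 months or reporting periods of discontinuation within last 18 months". Participants must also be people who "are interested in reducing frequency of stimulant use and improving ART adherence". Neither criterion requires a viral load above 200 copies/mL at enrolment, and the discontinuation route requires no raised viral load at all.
- **Test** (Analysis Plan, Quantitative Evaluation). "We will use the McNemar test to compare the proportion of participants with HIV viral loads less than 200 copies/mL before and after CM participation". No restriction to, or split by, status at entry is stated.
- **Missing data** (Evaluation Frameworks and Outcomes, Quantitative Evaluation). The plan is to report missing data and to "impute missing viral load data as >200 copies/mL".
- **Purpose and rank** (same section). The effectiveness metrics ask whether behaviour changed, "leading to reduced stimulant use, improved ART adherence, and undetectable HIV viral loads". "Our secondary outcome is preliminary effectiveness"; the primary outcome is visit attendance.

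The end value is the recorded viral load nearest to the last attended visit, taken from the medical record (Assessment and Data Collection). The before value is described in two ways. Assessment and Data Collection refers to the viral load before participation, while Table 2 and Recruitment and Informed Consent name the last detectable viral load.

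**The concern.** McNemar's test uses only participants whose status changes. Someone below 200 copies/mL at entry has no room to gain, so that person either stays unchanged or becomes a loss.

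The imputation rule acts differently by entry status. With no end value, a participant viremic at entry is coded viremic again and drops out of the test statistic. A participant suppressed at entry is coded as having lost suppression and counts directly against a gain.

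The net change therefore depends partly on how many suppressed people enrolled and how many of them lack an end value. A null or small result could mean that few viremic participants responded, or that a good response was masked by missing records. The pooled figure cannot tell these apart, yet the Discussion expects this pilot to inform larger trials.

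**Working it through.** The article gives no power, effect size, significance level or share suppressed at entry for this test, so there is no stated figure to reproduce. The calculation below shows how far the mechanism can move the result.

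**Inputs**
- N = 40, from "we aim to recruit approximately 40 participants".
- Response of 50% among viremic participants with an end value: assumed. The article's only related figure is more than 50% suppression within 6 months among viremic patients in one host clinic.
- Split at entry of 20 viremic/20 suppressed or 30/10: assumed.
- Missing end values m = 0, 10, 20 or 30% in both groups: assumed.
- No suppressed participant truly worsens, so every loss is an imputed one: assumed, to isolate the mechanism.
- Two-sided exact McNemar test at 0.05: assumed.

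**Formulas**
- Gains b ~ Binomial(n_viremic, 0.5 × (1 − m)).
- Losses c ~ Binomial(n_suppressed, m) under the plan's rule; c = 0 without imputed losses.
- Net change = (expected gains − expected losses) / 40.
- p = min(1, 2 × P[Binomial(b + c, ½) ≤ min(b, c)]).
- Chance of a significant gain = sum of the probabilities of all (b, c) with b > c and p ≤ 0.05.

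**Results, 20 viremic/20 suppressed**

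| Missing | Expected gains v losses | Net change | Chance, plan's rule | Chance, no imputed losses |
|---|---|---|---|---|
| 0% | 10 v 0 | +25.0 points | 98% | 98% |
| 10% | 9 v 2 | +17.5 points | 46% | 94% |
| 20% | 8 v 4 | +10.0 points | 9% | 87% |
| 30% | 7 v 6 | +2.5 points | 1% | 75% |

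Taking the 20% row:
- Expected gains are 20 × 0.5 × 0.8 = 8 and expected losses are 20 × 0.2 = 4.
- The net change is (8 − 4)/40 = +10 points.
- Eight gains against four losses give p = 0.39. Eight against none give p = 2 × (½)^8 = 0.008.

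**Results, 30 viremic/10 suppressed.** Under the plan's rule the chance is 96%, 77% and 43% at 10, 20 and 30% missing.

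**N = 37, as recruited (19/18 split).** The chance is 45%, 10% and 1%, much as for 40.

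**What drives the fall.** In the 20/20 split the chance is 98% with nothing missing. At 20% missing it is still 87% once imputed losses are removed. The drop from 98% to 87% comes from viremic participants who lack an end value. The drop from 87% to 9% comes from the imputed losses. Suppressed participants who stay suppressed dilute the change in proportion but do not count against the test.

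**The case against.** The strongest case on the other side has five parts.

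- **The cause is the imputation rule, not the 18-month window or pooling.** This stands. With no missing end values and no true losses, the pooled test does well even with half the sample suppressed at entry.
- **The missing rate and suppressed share are unsupported.** This also stands. End values come from routine records with no stated window, so few may be missing. The figures above are ranges, not predictions.
- **Net suppression is a legitimate target.** True. These are near-daily stimulant users with a recent adherence problem, and real loss of suppression among them is information. That argues for keeping the pooled test. It does not justify leaving real and imputed losses undistinguished.
- **A viremic-only figure has the opposite fault.** It can only rise, and in a single arm, selection on raised values invites regression to the mean. The host clinic's rate of more than 50% is reported without being attributed to contingency management. This stands, and it limits the remedy.
- **The direction is not fixed.** If the last detectable viral load were used as the before value, currently suppressed people could be coded viremic and counted as gains. This stands, and it is why the before value must be settled first.

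A reader might infer that the entry rule admits people who are currently adherent and that the trial cannot then show whether adherence improved. The documents do not support this. One suppressed value does not establish adherence, and adherence is also assessed by weekly tenofovir tests reported each week and cumulatively.

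**Conclusion.** The concern holds in limited form. Because entry does not require current viremia, the missing-as->200 rule acts in one direction on participants suppressed at entry, and the single pooled test sets those imputed losses against real gains. Under the assumed 20/20 split and 50% response, the chance of a significant gain at 20% missing is 9% under the plan's rule and 87% without imputed losses. With 10 suppressed at entry instead of 20, it is 77% under the plan's rule.

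These sizes rest on an assumed suppressed share, missing rate and response, on no true loss of suppression, and on reading the before value as the most recent one. If few participants were suppressed at entry, or few end values are missing, the effect is small.

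The stronger reading, that the 18-month lookback or pooling is itself the error, is not supported: the illustrated collapse comes almost entirely from imputed losses. This is a secondary endpoint of a pilot, and the attendance outcome is untouched.

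**What to change.** Keep eligibility and the pooled McNemar comparison as planned. Beside it, add:

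1. Among participants at or above 200 copies/mL at their most recent pre-enrolment viral load, the proportion reaching below 200.
2. Among participants below 200 at entry, the proportion remaining below 200.
3. In each group, an exact 95% interval and separate counts of observed and imputed end values.
4. An observed-data McNemar test as a sensitivity analysis.

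State that the before value is the most recent pre-enrolment viral load, not the last detectable one, and reconcile Table 2 and the recruitment text with this. Present the two groups together. Neither alone should be the main effectiveness figure, for the reasons given under the objection. Since the article says quantitative analysis had concluded by June 2025, label the split as an addition to the planned comparison.

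In the 20/20, 20%-missing example the display would read as follows:
- Newly suppressed: 8/20 with imputation (40%, 95% CI 19% to 64%) and 8/16 observed (50%, 25% to 75%).
- Maintained: 16/20 with imputation (80%, 56% to 94%) and 16/16 observed (100%, 79% to 100%).

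The reader then sees at once that all four losses are imputed.

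The cost is two table rows and one sensitivity test, provided the most recent pre-enrolment value is on file or can be taken from the medical record. The downside is small denominators and wide intervals, as the example shows.
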